### Program assessment and intervention fidelity

The DOHP facilitators will receive training, a structured manual/protocol and regular supervision (fortnightly with clinical investigators) to discuss any concerns and to ensure standardised delivery of the intervention. Any issues raised by participants can also be discussed at supervision meetings. Sessions will be audio recorded and rated by members of the research team to assure fidelity of the intervention (i.e. does the content of each session accurately reflect the stated content and session plan). Further, an expert of OHP not part of the research team will also randomly sample 10 % of the case notes to ensure sessions conducted comply with OHP session content and procedures. Any variations from the protocol will be fed back to facilitators.

Post-intervention focus groups will be held for clinicians and for participants. The purpose of the focus groups is to gain an in-depth understanding of their experiences of the DOHP, advantages and disadvantages of conducting the DOHP within existing services (for service providers), and suggestions for further components to include or to exclude.

### Statistical analyses

Intention-to-treat analysis will be employed to prevent overestimation of intervention efficacy. Categorical variables will be analysed using chi-squared tests (or Fisher’s exact test for small samples). A mixed-effects model, repeated measures (MMRM) approach will be used to examine the longitudinal profile of the two primary outcome measures at the three time points (3, 6 and 12 months post-baseline). For all MMRM analyses, baseline scores will be used as covariates and the models will include prespecified fixed effects of treatment, clinician and time, in addition to treatment-by-time and treatment-by-clinician interactions. Appropriate adjustments for multiple primary (depression and anxiety) tests will be made, i.e. Bonferroni correction to ensure the risk of type I error is maintained at 5 %. The potential impact of any additional care received by some participants will be assessed in a separate regression analysis using analysis of covariance.

Secondary analyses using analysis of covariance will be conducted to compare change scores during treatment and follow-up points for primary, secondary and process outcomes using the fixed, continuous covariate of baseline score as well as the categorical fixed effects of treatment group, clinician and treatment-by-clinician interactions. Following this, all secondary outcome measures will be assessed, as per above using first a MMRM and then assessing change scores.

Although the attrition rate is not expected to vary by group (intervention vs usual care), we will attempt to identify key predictors of attrition status (i.e. demographic or clinical baseline characteristics) and test for differences between groups. Assuming the data are missing at random, several procedures offer effective approaches that may attenuate attrition. For example, multiple imputation procedures that utilise the expectation-maximization (EM) algorithm with bootstrap estimates of standard errors will be used. A maximum likelihood model with time as a random variable will allow the use of all available data from all assessments, reducing bias and increasing power [40]. Application of these procedures has been shown to provide unbiased estimates, even in the face of substantial missing data [41].

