### Participants

A minimum of 96 patients initiating dialysis will be recruited into the study. The type of dialysis is haemodialysis, peritoneal dialysis or home dialysis, or collectively known as ‘dialysis’. The following criteria must be met for inclusion in the study: (1) diagnosis of near ESKD confirmed by medical records; (2) expected to commence maintenance dialysis for the first time in the next 3 months or commencement of dialysis in the past 3 months; (3) aged 18 or above; and (4) able to converse in English without an interpreter. Exclusion criteria are: (1) presence of developmental disability or amnestic syndrome impairing their ability to learn from the intervention; (2) participants returning to dialysis following a failed renal transplant; and (3) comorbid serious illness as defined by the treating physician. Individuals who are seeking a mental health professional or taking psychotropic medications will not be excluded from participating.

Power was calculated to detect a medium effect size of *d* = 0.40 using a sample size formula comparing time-averaged differences for continuous outcomes in repeated measurement studies [27]. The power calculations assumed the following: (a) two primary outcome measures (HADS anxiety and depression severity scores); (b) four assessment points (i.e. baseline, 3, 6, and 12 months); (c) a between-repeated measures ρ = 0.70; (d) a study-wide type I error of 0.05 (i.e. a single test α of 0.05 ÷ 5 or 0.01); (f) a type II error rate (β) of 0.20 (power of 0.80); and (g) two-tailed statistical tests. The within-subject correlation (0.70) was based upon a previous OHP trial that demonstrated high correlations over time [22]. The power analysis indicated that 38 participants would be required in each group. Allowing for an attrition rate of 20 %, a total of 96 participants, or 48 in each arm, will be recruited.

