#### Randomisation and blinding

Following the initial screening and gaining of consent, participants will be allocated to either intervention or control group via a computer-generated block randomisation sequence created by an independent person not directly involved in the study. Due to the nature and length of the intervention, it is not possible to blind either patient or investigator to the intervention allocation.

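### The prespecified models omit whether dialysis has started at entry, although entry spans six months around that start; adjusting for it could gain a little precision

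*Protocol article*

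**What the plan says.** Under Participants, the Protocol article sets the entry window as "expected to commence maintenance dialysis for the first time in the next 3 months or commencement of dialysis in the past 3 months". General design times the assessments from baseline (3, 6 and 12 months later), not from the first dialysis session.

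Under Statistical analyses, the primary model is a mixed model for repeated measures on the HADS depression and anxiety scores. On covariates it says "For all MMRM analyses, baseline scores will be used as covariates", and it adds "prespecified fixed effects of treatment, clinician and time, in addition to treatment-by-time and treatment-by-clinician interactions". The secondary analyses of covariance use the baseline score and the "categorical fixed effects of treatment group, clinician and treatment-by-clinician interactions". The only patient characteristic in either list is the baseline score of the outcome. Whether dialysis has started, or how long ago, appears in neither.

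**The concern.** Baseline HADS is measured before dialysis in some participants and after its start in others. A single baseline term treats the two as the same anchor, although the first group still has the start of treatment ahead of it. Because visits run from baseline, the same visit falls at different points of the dialysis experience.

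The article gives reason to think this could matter. Its Background describes the first year of dialysis as especially hard, and it singles out depressive symptoms soon after dialysis starts when discussing withdrawal from treatment. If status carries information about later HADS that the baseline score does not, leaving it out keeps explainable variation in the residual. In a trial planned around 38 evaluable participants per arm, that makes the treatment estimate somewhat less precise than it could be. Since status is established by an inclusion criterion, the information is available for everyone.

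**Working it through.** **Timing.** Let s be months on dialysis at baseline, from -3 to +3 under the entry criterion if those not yet started begin when expected. Time on dialysis at a visit is s plus the visit month.

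| Visit | s = -3 | s = 0 | s = +3 |
|---|---|---|---|
| 3 months | 0 | 3 | 6 |
| 6 months | 3 | 6 | 9 |
| 12 months | 9 | 12 | 15 |

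The outer columns are the extremes; most participants lie between them. At the last visit, those not started at entry are at 9 to 12 months and those already started are at 12 to 15.

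**Inputs from the article (Participants).** Effect size 0.40; within-person correlation 0.70; 38 evaluable per group; 20% attrition; single-test alpha 0.01, two-sided. The model uses three follow-up visits. Statistical analyses describes a Bonferroni correction for two primary tests, which is 0.05/2 = 0.025, so both levels are shown.

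**The plan's own figures.** The attrition step reproduces: 38/0.8 = 47.5, so 48 per arm and 96 in total. The 38 does not follow from the time-averaged formula with the stated inputs: 2(2.576 + 0.842)² × (1 + 3 × 0.70)/(4 × 0.40²) = 113.1 per group. That is a separate matter. Here 38 is used only as the planned evaluable number.

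**Assumptions, not in the documents.** Share on dialysis at entry p = 0.5. Status effect on follow-up HADS, given baseline, g = 0.2 to 0.4 SD.

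**Residual variance.** For the mean of three visits adjusted for baseline, in SD² units: (1 + 2 × 0.70)/3 - 0.70² = 0.80 - 0.49 = 0.31. Standard error of the treatment effect: sqrt(2 × 0.31/38) = 0.128 SD.

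**Share of residual variance due to status.** R² = p(1-p)g²/(0.31 + p(1-p)g²), where p(1-p) = 0.25. The standard error falls by 1 - sqrt(1 - R²). Power is Φ(0.40/SE - z), with SE = sqrt(2 × 0.31 × (1 - R²)/38) and z = 2.576 for alpha 0.01 or 2.241 for alpha 0.025.

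| g (SD) | R² | SE shorter by | Power, alpha 0.01 | Power, alpha 0.025 |
|---|---|---|---|---|
| 0 | 0 | 0 | 71.1% | 81.3% |
| 0.2 | 3.1% | 1.6% | 72.8% | 82.7% |
| 0.3 | 6.8% | 3.4% | 74.8% | 84.2% |
| 0.4 | 11.4% | 5.9% | 77.4% | 86.1% |

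The gain is 1.7 to 6.3 points at 0.01 and 1.3 to 4.8 points at 0.025.

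**Sensitivity to the share.** With p = 0.3 or 0.7, p(1-p) = 0.21, and R² is 2.6% to 9.8% over the same range of g. The 50% share is the most favourable case.

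**Price of the covariate.** Under random allocation of 76 people, the expected squared correlation of arm with a baseline factor is 1/75 = 1.3%. A status term that predicts nothing would inflate the variance by about that much. The figures above are before this deduction, so at g = 0.2 the net gain is small.

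**The case against.** The strongest objection is that nothing here is a mistake: omitting an optional covariate is a design choice, and the premise that it is prognostic is thin. The Background contrasts the first year of dialysis with later years. It does not compare patients just before the start with patients just after it, and both groups spend most of follow-up within their first year. The remark on early depressive symptoms concerns withdrawal from dialysis, not the course of HADS. No passage shows that status predicts follow-up HADS once baseline HADS is in the model. This stands, and it is why the effect is given only as an assumed range.

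The omission cannot simply be put down to an unseen analysis plan, because the article itself names its model terms as prespecified.

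A reader might infer four stronger points that the documents do not support.

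- **That allocation was unstratified.** The article describes a "computer-generated block randomisation sequence created by an independent person not directly involved in the study" and names no stratification factor. In a condensed article that is silence; a factor could sit in the full protocol.
- **That the omission biases the result.** It does not in expectation, and type I error is not affected.
- **That chance imbalance is a further harm.** At 38 per arm and a 50% share, the 95% range of imbalance is 1.96 × sqrt(0.5/38), about 22 points either way, which at g = 0.2 to 0.4 moves the estimate by 0.045 to 0.09 SD. That is the same loss in another form: the unadjusted standard error already includes random imbalance, so it must not be added to the variance share.
- **That modality should be adjusted for too.** No eligibility criterion concerns modality, and nothing in the article supports an effect of it on HADS.

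**Conclusion.** The point holds as a minor, optional improvement. The entry window, the timing from baseline and the absence of dialysis status from the listed terms are all plain in the text. The cost is precision only: about 3% to 11% of residual variance, 1.5% to 6% of the standard error, and roughly 1 to 5 power points at the 0.025 level (somewhat more at 0.01), before the small price of the extra term. These figures rest on an assumed 50% share on dialysis at entry and an assumed 0.2 to 0.4 SD effect beyond baseline HADS, set against the planned effect of 0.40. If status is not prognostic given baseline, there is nothing to gain. The validity of the randomised comparison is not in question.

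**What to change.** In Statistical analyses, add dialysis status at randomisation (not started or started) as a prespecified covariate: in the primary mixed model with its interaction with time, and in the analyses of covariance as a main effect. Fix this before any outcome data are seen by arm, since adding it after an imbalance appears would look data-driven. Recruitment was still under way at submission. No change to the randomisation is needed.

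The cost is one sentence. Status follows from the second inclusion criterion, so no new data collection is needed beyond recording it as of the date of randomisation. With three follow-up visits, the main effect and its interaction with time use three parameters in the mixed model (1 + 2), and the main effect uses one in each analysis of covariance. That is a modest charge on about 76 evaluable participants in models that already carry clinician and treatment-by-clinician terms.

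### A baseline-by-time term in the HADS mixed model would be a cheap safeguard against late-visit bias that arises only under arm-differential, baseline-dependent dropout

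*Protocol article*

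**What the plan says.** The Statistical analyses section of the protocol article sets out one specification that covers every MMRM it plans: "baseline scores will be used as covariates and the models will include prespecified fixed effects of treatment, clinician and time". Two interactions are also named, that of treatment with time and that of treatment with clinician. The model is used "to examine the longitudinal profile of the two primary outcome measures at the three time points (3, 6 and 12 months post-baseline". Treatment may therefore act differently at each visit, but the listed terms do not let the baseline score do so.

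On dropout, the same section assumes data missing at random and does not expect the attrition rate to differ by arm. It says the team will try to "identify key predictors of attrition status (i.e. demographic or clinical baseline characteristics" and will test for group differences. It also says its missing-data procedures have been shown to be unbiased even with substantial missing data.

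The Participants section targets *d* = 0.40, "using a sample size formula comparing time-averaged differences for continuous outcomes in repeated measurement studies", with one within-subject correlation: "The within-subject correlation (0.70) was based upon a previous OHP trial that demonstrated high correlations over time". It gives no correlations by visit, and neither section singles out 12 months as the primary time point.

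**The concern.** A baseline score often predicts an early follow-up score better than a late one. Here baseline may fall up to 3 months before or after dialysis starts, so some weakening by 12 months is plausible. A single pooled slope then over-corrects for baseline at 12 months. If the participants still observed at 12 months differ in baseline HADS between the arms, this over-correction enters the treatment difference. A likelihood analysis under missing at random is protected only when its model for the means is right, and a wrongly shared slope can break that. At stake are the late part of the HADS profile and, less so, the average over visits.

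**Working it through.** The plan has no figure of its own on this point, so there is none to reproduce.

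**Inputs from the article.** Model terms as quoted; effect 0.40 SD; correlation 0.70; attrition 20%; 48 per arm (38 / 0.8 = 47.5, rounded up), 96 in total.

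**Assumptions, not in the article.**
- Baseline correlations at 3/6/12 months of 0.70/0.65/0.60 (mild decay), 0.70/0.60/0.45 (moderate decay) or 0.70 throughout.
- Correlation of 0.70 between follow-up visits, unit variances, and a true effect of -0.40 at each visit.
- Dropout log-odds of -1.6 + 1.2x in the DOHP arm, where x is standardised baseline HADS. In control the slope is +1.2 (same dependence), 0 (one arm only) or -1.2 (opposite directions). The first missed visit is equally likely to be 3, 6 or 12 months.
- Clinician terms are left out.

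**Step 1: when the error cancels.** Let the true slope at visit t be b_t and the pooled slope b. The model leaves (b_t - b)x unexplained at visit t. Writing m_arm for the mean baseline of those still observed, the error in the treatment difference is approximately

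bias at t = (b_t - b) × (m_DOHP - m_control).

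It is zero if the slope is constant (first factor) or if dropout depends on baseline in the same way in both arms (second factor). Both factors must be non-zero for bias.

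**Step 2: by hand at 12 months.** With dropout probability p(x), those still observed have mean baseline -E[x p(x)] / (1 - E[p(x)]). For log-odds -1.6 + 1.2x this is about -0.21, with 22% dropout. With slope 0 it is 0, with 17% dropout. The fitted pooled slope was about 0.66 under moderate decay and 0.67 under mild decay.
- Moderate, one arm: (0.45 - 0.66) × (-0.21 - 0) = 0.044
- Moderate, opposite: (0.45 - 0.66) × (-0.21 - 0.21) = 0.088
- Mild, one arm: (0.60 - 0.67) × (-0.21 - 0) = 0.015
- Mild, opposite: (0.60 - 0.67) × (-0.21 - 0.21) = 0.029

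**Step 3: by simulation.** This used a maximum-likelihood MMRM with unstructured covariance and 8 × 60,000 simulated patients per row. Simulation error is at most 0.004. The two models were fitted to the same data, so their difference is more precise than that. Each pair is without / with baseline-by-time.

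| Correlations | Dropout on baseline | 12 months | Visit average |
|---|---|---|---|
| 0.70/0.70/0.70 | same | -0.401 / -0.401 | -0.401 / -0.401 |
| 0.70/0.70/0.70 | opposite | -0.398 / -0.398 | -0.397 / -0.397 |
| 0.70/0.65/0.60 | same | -0.405 / -0.404 | -0.403 / -0.403 |
| 0.70/0.65/0.60 | one arm | -0.381 / -0.396 | -0.390 / -0.396 |
| 0.70/0.65/0.60 | opposite | -0.369 / -0.402 | -0.390 / -0.402 |
| 0.70/0.60/0.45 | same | -0.398 / -0.397 | -0.398 / -0.398 |
| 0.70/0.60/0.45 | one arm | -0.358 / -0.403 | -0.384 / -0.401 |
| 0.70/0.60/0.45 | opposite | -0.313 / -0.405 | -0.367 / -0.402 |

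The differences between models are 0.015 to 0.092 SD at 12 months and 0.006 to 0.035 SD for the average, in line with Step 2. Repeat runs under moderate decay gave -0.350 to -0.36 (one arm) and -0.309 to -0.32 (opposite) at 12 months without the term. Steeper assumed slopes of 0.8/0.6/0.3, with dropout log-odds changing by 1 per SD, gave biases of 0.071 and 0.145. With the same dependence in both arms the bias was -0.002.

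**Step 4: precision at 96 participants.** The 12-month standard error without and with the term was 0.160 and 0.161 under a constant slope, and 0.211 and 0.207 under moderate decay. Even the 0.092 shift is under half a standard error (0.092 / 0.207 = 0.44).

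**The case against.** The strongest case against raising this has five parts.

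- **The conditions are not shown.** The only correlation in the article is a single 0.70, and attrition is not expected to differ by arm. This stands: the bias is conditional. The expectation concerns the rate of attrition, however, and equal rates do not imply equal dependence on baseline. In the opposite-directions case above, both arms lose 22%. The trial is open-label and only one arm carries nine sessions with tasks in between, so a difference in who leaves is possible.
- **Twelve months is not the named target.** This stands too. The power calculation concerns a time-averaged difference, for which the bias is at most about 0.035 SD in the range examined.
- **A second analysis partly covers it.** The article also plans analysis of covariance on change scores. If fitted visit by visit, each has its own baseline slope. That is a useful cross-check, but it does not alter the primary model.
- **It may be detail for the analysis plan.** The article does not say that other terms are excluded. Yet it names the interactions one by one for every MMRM, so this is a stated specification that can be improved.
- **The article only looks for predictors of attrition.** Correct. A reader might infer that the plan expects baseline characteristics to predict dropout, but the text announces a search, not an expectation.

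**Conclusion.** The listed terms do hold the baseline slope constant over the three visits. Bias follows only if the slope decays and dropout depends on baseline HADS differently by arm. It is then about 0.015 to 0.09 SD of a 0.40 SD effect at 12 months, and about 0.005 to 0.035 SD for the visit average, at about 20% dropout. These sizes rest on assumed correlations and dropout models and on leaving out the clinician terms. In the scenarios run, higher-baseline DOHP participants drop out more and the effect is understated; reversing that pattern would reverse the sign.

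A reader might infer that the 12-month effect is biased whenever dropout depends on baseline HADS. That does not follow. With the same dependence in both arms the error cancels, as Step 1 and the table show. The point is an optional, cheap improvement and not an error in the plan.

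**What to change.** Add baseline-by-time to the fixed effects listed for the HADS MMRM and for each secondary MMRM with repeated follow-up. Let the baseline score have visit-specific slopes in any imputation model too, so that the restriction does not return there.

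The cost is one phrase and two degrees of freedom per model (three slopes in place of one), with no new data. If the slope proves constant, essentially nothing is lost.

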### Intervention: DOHP

The DOHP is delivered in nine (8 + 1 booster session) sequential sessions based on a structured workbook. The workbook is central to learning, (i) providing detailed information on the contents of each session and (ii) acting as a health journal where participants can record key dates, appointments, contacts and medication details. Participants are encouraged throughout the program to identify areas of kidney disease or specific concerns upon which they would like to focus. Sessions are approximately 1 hour in duration and held weekly, apart from the ‘booster’ session, which is held 3 months after session 8. Each participant will be allocated to one OHP trained facilitator who will administer the suite of questionnaires, taking approximately 25 minutes to complete, and conduct the intervention. Learning is cumulative with each session designed to build on the previous session including tasks to complete between sessions, such as coping strategies (e.g. breathing exercises).

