A health professional (e.g. nurse, psychologist) trained in the collaborative therapy approach (2-day workshop plus regular supervision and fidelity checks) will facilitate each session. The facilitator will draw on CKD/ESKD-specific information in concordance with individual circumstances. Examples include coping strategies for addressing anxiety related to self-monitoring of blood pressure, availability of community supports, and dealing with the stress of adapting to ESKD and initiating dialysis. Emphasis is placed on the collaboration between facilitator and participant to achieve goals that stem from the participant’s intrinsic concerns and needs. Health promotion is also a major focus, hence the facilitator will encourage participants to identify early warning signs of stress and illness and integrate healthy coping strategies to prevent the build-up of stress. In conjunction with the multidisciplinary team, facilitators will coordinate visits and discuss and arrange referrals to other services depending on participant needs. Further, if at any time during the study a participant identified severe anxiety and/or depression or suicidal ideation they will be contacted by a senior clinician of the research team and where relevant, referred to an appropriate mental health service. Patient participation may be discontinued based upon self-request and/or feedback from the referred treating mental health service. Participants residing in rural and regional areas will have the option of participating in sessions via telephone or Skype (depending on patients’ access to the internet).

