### Standard care

Participants randomised into the standard care condition will receive medical care consistent with patients who have ESKD. This will include regular medical appointments with medical staff, diagnostic tests (e.g. blood glucose levels) and access to treatments based upon disease status and recommendations by treating hospital staff.

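### The prespecified models contain fixed clinician and treatment-by-clinician terms, yet facilitators are described only for the DOHP arm, so on that reading the listed terms cannot all be estimated and the treatment contrast is left undefined

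*Protocol article*

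**What the plan says.** In Statistical analyses, the MMRM for the two HADS outcomes adjusts for the baseline score and includes "prespecified fixed effects of treatment, clinician and time, in addition to treatment-by-time and treatment-by-clinician interactions". The section applies this to all MMRM analyses. The ANCOVA of change scores has the same structure, with "categorical fixed effects of treatment group, clinician and treatment-by-clinician interactions". Secondary outcomes go through both models in turn, so the clinician terms appear in every efficacy analysis.

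The word clinician is not defined there. The nearest description is under Intervention: DOHP: "Each participant will be allocated to one OHP trained facilitator who will administer the suite of questionnaires". That sentence goes on to say that the same person conducts the intervention. The same section says that a health professional "trained in the collaborative therapy approach (2-day workshop plus regular supervision and fidelity checks) will facilitate each session". Program assessment and intervention fidelity also refers to facilitators as those who deliver the DOHP.

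For the other arm, Standard care says: "Participants randomised into the standard care condition will receive medical care consistent with patients who have ESKD". It names medical and treating hospital staff and no facilitator. Under Randomisation and blinding, participants are "allocated to either intervention or control group via a computer-generated block randomisation sequence"; neither stratification by clinician nor a rule for assigning one is stated.

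**The concern.** A clinician effect and a treatment-by-clinician interaction can be separated from treatment only if the same clinicians have patients in both arms. If the clinician is the DOHP facilitator, controls have none. The treatment indicator is then the sum of the facilitator indicators, and the interaction columns repeat the facilitator columns.

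Software will still run such a model by dropping columns. What is printed as the treatment effect then depends on which columns were dropped and how controls were coded. The two primary outcomes would be judged on a quantity fixed by coding rather than by the plan, and the same holds for every secondary model. The terms are called prespecified, so this is a stated feature of the model and not a detail left for later.

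**Working it through.** **Inputs.** From the article: three post-baseline visits (3, 6 and 12 months), the model terms, 48 per arm recruited, 38 per arm after attrition, correlation 0.70 and d = 0.40. Assumed: the number of facilitators K, because the article gives none; K = 2, 3, 4 and 6 are shown. The power figures use a two-sided level of 0.05/2 = 0.025, which is Bonferroni for the two primary outcomes as in Statistical analyses.

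The article's 38 per group serves here only as the number analysed. The stated inputs do not reproduce it: 2(2.576 + 0.842)² × [1 + 3(0.70)] / (4 × 0.40²) = 113.1 per arm at a single-test level of 0.01. That is a separate matter and does not affect the rank results.

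**1. Clinician only in the DOHP arm.** Intercept, treatment, K clinician columns and K interaction columns make 2K + 2. There are only K + 1 distinct cells (K facilitators plus control), so the rank is K + 1 and the deficiency is K + 1. Time and treatment-by-time add 4 columns and 4 to the rank. Baseline adds 1 to each and is left out.

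| K | Columns | Rank |
|---|---|---|
| 2 | 10 | 7 |
| 3 | 12 | 8 |
| 4 | 14 | 9 |
| 6 | 18 | 11 |

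The treatment coefficient is not estimable. This remains so without the interaction, where treatment and clinician need K + 2 columns for K + 1 cells. The mean of the facilitator cells minus the control mean is estimable throughout.

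**2. Controls coded to a reference facilitator.** The intercept, treatment and clinician terms now take 2K columns with rank K + 1, so the interaction is still not estimable. The treatment coefficient is estimable, but it compares the reference facilitator's patients with all controls. Its SE relative to the all-facilitator contrast is √[(K/n + 1/n)/(2/n)] = √[(K + 1)/2].

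| K | DOHP patients in the contrast (of 48) | SE ratio |
|---|---|---|
| 2 | 24 | 1.22 |
| 3 | 16 | 1.41 |
| 4 | 12 | 1.58 |
| 6 | 8 | 1.87 |

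**3. Clinician crossed with arm.** For K = 4, including time, there are 12 columns and the rank is 12. The model can be fitted. For the size of the effect, take the variance of the three-visit mean after baseline adjustment: (1 + 2 × 0.70)/3 − 0.70² = 0.31. Without clinician terms, SE = √(2 × 0.31/38) = 0.128 SD. Simulation with 4 facilitators gave 0.134 for the facilitator-averaged contrast and 0.266 for the contrast at the reference facilitator alone.

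- No clinician terms: 0.40/0.128 − 2.241 = 0.88, power 81%.
- Averaged over facilitators: 0.40/0.134 − 2.241 = 0.74, power 77%.
- Reference facilitator only: 0.40/0.266 − 2.241 = −0.74, power 23%.

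**4. Facilitator variation left out of the SE (illustration only).** If facilitators differ with variance v (share of total) in the DOHP arm, the variance of the contrast grows from 0.0163 to 0.0163 + v/K. For K = 4 and v = 0.02 it is 0.0213, and a nominal 2.5% test has a true level of about 5.0%. For K = 3 and v = 0.05 it is 0.0330, and the level is about 11.5%. Simulation gave 4.3% and 10.5% for the same two cases. Both K and v are assumed.

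**The case against.** The strongest reply is that nesting is an inference. The model says clinician, not facilitator. Controls complete the same questionnaires, so a facilitator may administer them in both arms, and writing a treatment-by-clinician interaction suggests that the authors saw clinician as crossed with arm. If so, step 3 applies and the model has full rank. This possibility stands and limits the certainty of the point. Against it, the sentence that allocates a facilitator is under the intervention heading and has the same person conduct the intervention, and Standard care gives controls none.

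Three stronger readings are tempting, and the article does not support them.

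- A reader might infer that the treatment effect cannot be identified at all. Even when nested, the facilitator-averaged contrast is estimable. What fails is the main-effect coefficient and the interaction as listed.
- A reader might infer that power collapses from 81% to 23%. That figure belongs to the crossed case, and only if one reference-coded coefficient is read as the result. It also averages over visits but not over facilitators, which is an uneven comparison. With averaging over both, the loss is about 4 percentage points.
- A reader might infer that the true error of the primary tests is 4% to 10%. The article gives neither the number of facilitators nor their variance, and if facilitators do not differ there is no inflation. Fixed effects also answer a legitimate narrower question, about the facilitators actually used in this single-centre trial.

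It can also be said that naming a contrast is ordinary SAP content. That is fair for the contrast alone, but the article itself fixes the model terms, and on the likelier reading they do not fit the design.

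**Conclusion.** The point holds as a specification error in the primary model, repeated in all secondary models. If facilitators serve only the DOHP arm, the listed terms are rank deficient for any K of 2 or more, the interaction cannot be estimated, and the treatment coefficient is aliased or is a one-facilitator contrast with an SE 1.22 to 1.87 times that of the overall contrast (K = 2 to 6, equal caseloads). The usable estimate is the facilitator average minus control, which the article does not name.

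The conclusion rests on reading clinician as the DOHP facilitator. If clinician is crossed with arm, what remains is an undefined term and an unnamed contrast, with a small power cost (81% to 77% under the assumptions in step 3). The error-rate figures in step 4 show a direction and are not an estimate for this trial. Correction is still needed before analysis, because on the likelier reading the stated primary model cannot be fitted as listed.

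**What to change.** Remove the fixed clinician and treatment-by-clinician terms from the primary MMRM, the change-score ANCOVA and the secondary models. Define the treatment effect as the overall DOHP-minus-control contrast. Allow for facilitator clustering by a random effect in the DOHP arm only (a partially nested model), with Kenward-Roger or Satterthwaite degrees of freedom, and describe variation between facilitators descriptively.

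If a clinician does serve participants in both arms, say who that is, how participants are assigned, and prespecify the treatment effect averaged over facilitators.

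The change is to analysis wording and model specification. It requires no change to recruitment or care. The downside is a somewhat wider interval and, with few facilitators, an imprecise estimate of their variance.
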